# CLEAR – clozapine in early psychosis: study protocol for a multi-centre, randomised controlled trial of clozapine vs other antipsychotics for young people with treatment resistant schizophrenia in real world settings

**DOI:** 10.1186/s12888-023-05397-1

**Published:** 2024-02-14

**Keywords:** Clozapine, Treatment resistant psychosis, Children and young people, Early onset schizophrenia, Clinical trial

## Abstract

**Background:**

Clozapine is an antipsychotic drug with unique efficacy, and it is the only recommended treatment for treatment-resistant schizophrenia (TRS: failure to respond to at least two different antipsychotics). However, clozapine is also associated with a range of adverse effects which restrict its use, including blood dyscrasias, for which haematological monitoring is required. As treatment resistance is recognised earlier in the illness, the question of whether clozapine should be prescribed in children and young people is increasingly important. However, most research to date has been in older, chronic patients, and evidence regarding the efficacy and safety of clozapine in people under age 25 is lacking. The CLEAR (CLozapine in EARly psychosis) trial will assess whether clozapine is more effective than treatment as usual (TAU), at the level of clinical symptoms, patient rated outcomes, quality of life and cost-effectiveness in people below 25 years of age. Additionally, a nested biomarker study will investigate the mechanisms of action of clozapine compared to TAU.

**Methods and design:**

This is the protocol of a multi-centre, open label, blind-rated, randomised controlled effectiveness trial of clozapine vs TAU (any other oral antipsychotic monotherapy licenced in the British National Formulary) for 12 weeks in 260 children and young people with TRS (12–24 years old).

**Aim and objectives:**

The primary outcome is the change in blind-rated Positive and Negative Syndrome Scale scores at 12 weeks from baseline. Secondary outcomes include blind-rated Clinical Global Impression, patient-rated outcomes, quality of life, adverse effects, and treatment adherence. Patients will be followed up for 12 months and will be invited to give consent for longer term follow-up using clinical records and potential re-contact for further research. For mechanism of action, change in brain magnetic resonance imaging (MRI) biomarkers and peripheral inflammatory markers will be measured over 12 weeks.

**Discussion:**

The CLEAR trial will contribute knowledge on clozapine effectiveness, safety and cost-effectiveness compared to standard antipsychotics in young people with TRS, and the results may guide future clinical treatment recommendation for early psychosis.

**Trial registration:**

ISRCTN Number: 37176025, IRAS Number: 1004947.

**Trial status:**

In set-up. Protocol version 4.0 01/08/23. Current up to date protocol available here: https://fundingawards.nihr.ac.uk/award/NIHR131175#/.

## Introduction

Treatment resistant schizophrenia (TRS), defined by NICE and most other treatment guidelines as non-response to at least two different antipsychotic drugs (at least 1 of which should be a non‑clozapine second‑generation antipsychotic) [1], affects around one third of people diagnosed with schizophrenia [2]. TRS is associated with severe long-term consequences on social, educational and occupational functioning, with total treatment costs between three and eleven times that of schizophrenia that is responsive to standard treatment [3]. Treatment resistance in schizophrenia is strongly associated with age at illness onset, with onset before age 25 predicting higher risk of subsequent treatment resistance [4]. Clozapine is the only antipsychotic to have superior efficacy in TRS and is the treatment of choice in adults with TRS [5]. This is supported by evidence from randomised controlled trials [6, 7] although some doubt has been cast on the strength of this evidence [8]. Pharmacoepidemiological studies have demonstrated the superiority of clozapine over other antipsychotics in reducing readmissions [9], violent offending [10] self-harm [11] and all-cause mortality [12].

Most of the evidence for the superiority of clozapine over other antipsychotics derives from studies in chronic patients; a recent meta-analysis found the median age in trials of clozapine to be 39 years with a median length of illness of 16 years [8]. Delay in initiating clozapine is associated with poorer response, and earlier use of clozapine and fewer pre-clozapine antipsychotic trials have been found to be associated with better treatment outcomes [13, 14]. The evidence for the efficacy of clozapine in younger patients is sparse, although it suggests that clozapine is superior to other antipsychotics in people under 18 with TRS [15], and that younger age is associated with greater symptom reduction in clozapine-treated people [16]. A recent retrospective study showed that the vast majority of paediatric patients (95%) admitted with or started on clozapine during an acute psychiatric hospitalization remained on clozapine at discharge, suggesting that it may be clinically effective [17]. Furthermore, a Danish cohort study on early onset schizophrenia showed that the majority of patients (88.8%) prescribed clozapine were considered as having a favourable response since they continued to redeem clozapine prescriptions for more than 6 months [18]. However, there are significant limitations of naturalistic, observation data such as these, including that clinicians may be unlikely to stop clozapine treatment once started given a perception it is a treatment of last resort [19]. There is thus a clear need for larger scale clinical trials in younger patients.

Clozapine is reserved as a third line treatment because of its associated adverse effects, which are more numerous and severe than those of most other antipsychotics [20]. The most problematic is the rare but potentially fatal adverse effect of severe neutropenia [21]. In order to reduce the risk of agranulocytosis, in the UK and most other Western countries, monitoring of the patient’s full blood count is mandatory in clozapine-treated patients [22]. There is evidence that psychiatrists unfamiliar with clozapine are reluctant to prescribe it, and that blood testing in particular acts as a barrier [23]. This may particularly apply to child and adolescent psychiatrists, who rarely encounter TRS. Less than 0.5% of prescriptions for clozapine are in children and adolescents, and a survey of UK psychiatrists showed that only 40% of psychiatrists working in UK Child and Adolescent services have ever prescribed clozapine [24]. The probable superior efficacy of clozapine in younger patients must be balanced against its potentially inferior tolerability [25]. A recent literature review concludes that the risk–benefit ratio for clozapine use in young TRS patients is unclear, and that the question can only be resolved by conducting well powered studies that simultaneously measure safety and effectiveness [26].

The NICE guidance for schizophrenia and psychosis in adults (CG-178) and children (CG-155) recommend clozapine in patients whose illness has not responded to trials of at least two antipsychotics of adequate dose and duration. Nevertheless, the NICE Guideline Development Group (NICE Recommendation CG155/5) and the James Lind Alliance [27] have both identified the lack of evidence surrounding this recommendation, particularly with regard to overall cost-effectiveness. A well powered randomised controlled effectiveness trial is required to fill this gap. No such study has been completed to date, probably reflecting the difficulties of recruitment in this patient group. This trial will assess whether clozapine is more effective than treatment as usual (TAU: standard antipsychotics) in people below 25 years of age, at the level of clinical symptoms, patient rated outcomes, quality of life and cost-effectiveness.

The mechanisms underlying the efficacy of clozapine in TRS are not well understood [28]. Dopamine D2 receptor antagonism is the key mediator of efficacy for non-clozapine antipsychotics, but clozapine is a relatively weak dopamine D2 receptor antagonist, suggesting that its mode of action lies elsewhere [29]. Leading theories of schizophrenia pathogenesis include the interlinked processes of increased inflammation, oxidative stress and glutamate release [30, 31]. Preclinical research has shown that, compared to most other antipsychotics, clozapine may be particularly effective in reducing expression of proinflammatory cytokines (e.g. IL-6), increasing expression of anti-inflammatory cytokines (e.g. IL-10) [32, 33], has greater antioxidant effects [34–36], and can reduce brain glutamate [37–39]. Higher brain glutamate metabolite levels have been found in studies of patients with TRS [40–42], and reductions in glutamate have been observed during clozapine treatment [43]. The trial will incorporate a mechanistic study to investigate whether the efficacy of clozapine compared to TAU is linked to its actions on these pathways.

## Trial design

This is a multi-centre, open label, blind-rated, randomised, controlled effectiveness trial of clozapine vs TAU (i.e., compared with other antipsychotics of clinician’s choice) for 12 weeks in 260 children and young people with TRS (12–24 years old).

### Aim and objectives

The purpose of the trial is to assess whether clozapine is more effective than TAU (standard antipsychotics) in young people with TRS in real-world settings, over a 12-week period, at the level of clinical symptoms, patient-rated outcomes, quality of life and cost-effectiveness. The primary objective is to compare the treatments on the change in total Positive and Negative Syndrome Scale (PANSS) [44] score from baseline to 12 weeks. The secondary objectives are to compare the treatments on function, adverse effects, quality of life, subjective improvement, and cost-effectiveness.

In the CLEAR trial the following hypotheses will be tested:Primary hypothesis: clozapine will be more effective than TAU after 12 weeks of treatment as demonstrated by reduction in PANSS total scoresSecondary hypotheses:Clozapine will lead to a higher global improvement than TAU as measured by the CGI at 12 weeks, 24 weeks, and 52 weeksClozapine will lead to a better improvement in health-related quality of life than TAU as measured by EQ-5D-Y at 12 weeks, 24 weeks, and 52 weeksClozapine will be cost-effective compared to TAU at 12 weeks, 24 weeks, and 52 weeksThe prevalence of adverse effects in participants on the clozapine arm will be higher than TAU at 12 weeks as measured by the GASS-C, weight, and metabolic laboratory measurements (i.e., higher HbA1C and lipids)The clozapine arm will be more likely to remain on the same medication longer-term than TAU, as measured by medication use at 24 weeks and 52 weeks.Mechanistic hypotheses:Improvement in schizophrenia symptom severity during clozapine treatment compared to TAU will be mediated by anti-inflammatory and glutamatergic mechanisms. The biomarkers characterising these anti-inflammatory and glutamatergic mechanisms will include reductions in peripheral proinflammatory cytokines (e.g., IL-6), brain glutamate and rCBF, and increases in anti-inflammatory cytokines (e.g., IL-10) and peripheral and central oxidative defence (GSH) from baseline to 12 weeks.

### Trial flowchart

Figure 1 shows the trial flowchart. During the clinical trial (treatment period), participants will be allocated to either clozapine or TAU. After 12 weeks of treatment, participants will be able to continue or change treatment according to clinical needs and existing guidelines, and they will be followed up via phone or videocall whenever possible, otherwise case notes will be reviewed to assess longer-term outcomes. Schedule of enrolment, interventions and assessments are shown in the SPIRIT flow diagram (Fig. 2).

**Fig. 1 Fig1:**
[figure not shown]
Trial flowchart

**Fig. 2 Fig2:**
[figure not shown]
SPIRIT flow diagram: Schedule of enrolment, interventions, and assessments. *RA*: Research Assistant;
*CLZ*: clozapine; *PANSS*: Positive and Negative Syndrome Scale; *CGI-S*: Clinical Global Impression – Severity; *CGI-I*: Clinical Global Impression
– Improvement; *GASS-C*: Glasgow Antipsychotic Side-effects Scale for Clozapine; *EQ-5D-Y*: Youth version of the EQ-5D; *DAI-10*: Drug Attitude Inventory–10 items; *ReQoL-10*: Recovering Quality of Life Questionnaire; *EI-AD-SUS*: Early Intervention Adult Service Use Schedule;
*CRS*: Clinician Rating Scale

### Setting

We will recruit from NHS-funded secondary care, both inpatient and community settings, using a hub and spoke model, with 6 academic centres (King’s College London, University of Birmingham, Cardiff University, The University of Manchester, University of Oxford, University College London) coordinating approximately 30 NHS recruitment sites.

### Study population and eligibility criteria

We will recruit 260 children and young people from 12 to 24 years old with TRS as defined by NICE (CG178, Sect. 1.5.7.2). Inclusion and exclusion criteria are specified in greater detail in Table 1.

**Table 1 Tab1:** Inclusion and exclusion criteria

**Inclusion criteria**	**Exclusion criteria**
1. Age ≥ 12 and < 25 years at randomization 2. Meets criteria for schizophrenia or related disorder, in the range in the range ICD-10v2016 F20.x, F22.x-F29.x 3. Meets criteria for treatment resistance, defined as: a. Previous trials of at least two different antipsychotic drugs with adequate adherence (estimated < 20% missed doses), both treatment trials to exceed 6 weeks at therapeutic dose (≥ 600 mg chlorpromazine equivalent) b. At least 1 of these trials must be with a second-generation drug c. Failure to respond to NICE-recommended psychological treatment OR failure to engage in same 4. PANSS total ≥ 70, at least 2 items > 4 5. CRS > 3 6. Capacity to give informed consent OR has a legal representative able to give consent to the trial 7. English or Welsh language sufficient to participate	1. Psychosis predominantly caused by substance misuse 2. Pregnancy 3. Breastfeeding 4. Contra-indications to clozapine as listed in SmPC as follows: a. Hypersensitivity to the active substance or to any of the excipients b. Patients unable to undergo regular blood tests c. History of toxic or idiosyncratic granulocytopenia/ agranulocytosis (except for granulocytopenia/ agranulocytosis from previous chemotherapy) d. History of clozapine-induced agranulocytosis e. Impaired bone marrow function f. Uncontrolled epilepsy g. Alcoholic and other toxic psychoses, drug intoxication, comatose conditions h. Circulatory collapse and/or CNS depression of any cause i. Severe renal or cardiac disorders (e.g., myocarditis) j. Active liver disease associated with nausea, anorexia or jaundice, progressive liver disease, hepatic failure k. Paralytic ileus l. Clozapine treatment must not be started concurrently with substances known to have a substantial potential for causing agranulocytosis; concomitant use of depot antipsychotics is to be discouraged 5. Previous adequate trial of clozapine, as defined by TRIPP working group consensus guidelines, i.e. duration of at least 3 months following attainment of therapeutic plasma levels or a minimum dose of 500 mg/day (if no plasma level available) 6. CNS disorders (ICD-10 G00-26; G40-41, G45-46; G80-94, G97) 7. Concurrent medications with documented interactions with antipsychotics^a^ 8. Participation in a medicinal trial involving an unlicensed, investigational medical product within the last 3 month 9. Positive test for COVID-19 within the past 10 days 10. For participation in the substudy MRI scan only, standard contraindications to MRI at 3 Tesla such as ferromagnetic or electronic implants

*PANSS *Positive and Negative Syndrome Scale,* CRS *Clinician Rating Scale

^a^Defined as (1) strong Cytochrome P-450 CYP1A2 Inhibitors (i.e. fluvoxamine, abiraterone, midostaurin, enoxacin, ciprofloxacin, zafirlukast, Technetium Tc-99 m ciprofloxacin, furafylline, rofecoxib, quinidine, clinafloxacin, amiodarone, viloxazine) [45]; or (2) life-threatening or contraindicated combination (i.e. abametapir, domperidone, hydroxyzine, mizolastine, nirmatrelvir, ritonavir, sibutramine) [46]

### Interventions

During the 12 weeks of the trial, we will compare clozapine vs. TAU.

Intervention arm: Clozapine, oral, flexible dose within dose range defined by British National Formulary [47], at the discretion of the prescriber, for a minimum of 12 weeks. As clozapine has unpredictable pharmacokinetics with high heterogeneity in plasma concentration, depending on age, sex, smoking status, and genetics of the liver enzymes that metabolise it (especially CYP-1A2 and-2D6), enforcing a fixed dose would reduce the acceptability of the trial to patients and clinicians. It also requires titration over the first 2 weeks up to therapeutic doses to minimise postural hypotension, and the optimal balance between efficacy and adverse effects can only be achieved on an individual basis. The previously prescribed antipsychotic can be titrated down during the first 2 weeks of clozapine treatment and must be stopped within the first two weeks.

Control arm: Any oral antipsychotic other than clozapine, within licensed dose range defined by BNF [47], for a minimum of 12 weeks. The choice of antipsychotic will be agreed by the clinical team in collaboration with the participant, and the dose titrated to achieve the best balance between response and adverse effects.

### Outcomes

The primary outcome is the change in total blind rated PANSS total scores at 12 weeks from baseline.

Secondary outcomes include: blind rated change in overall Clinical Global Impression Scale (CGI) [48], clinician rated level of adherence (CRS) [49], adverse effects (GASS-C) [50], health-related quality of life (EQ-5D-Y) [51], subjective experience (DAI-10) [52], readmission rate, (EI-AD-SUS) [53], and change in PANSS sub-scale (positive, negative and general) [44]. We will also combine these outcomes (EQ-5D-Y and total PANSS score) with service use data (EI-AD-SUS) to compare treatments on cost-effectiveness.

Patients will be followed up for 12 months with the potential for further follow-up using clinical records for longer-term evaluations.

For the mechanistic study, outcomes include the change in brain glutamate, regional cerebral blood flow (rCBF) and GSH, and peripheral cytokines and GSH from baseline to 12 weeks.

### Assessments

#### Clinical trial

Centralised, remote, blind assessments by Research Psychiatrists will include:PANSS, the primary outcome. It is the most well validated standardised rating scale in clinical trials of psychosisCGI. It is simple and designed to capture the overall clinical judgement of an experienced clinician. CGI-Severity (CGI-S) will be assessed at baseline, and CGI-Improvement (CGI-I) will be assessed in the following visits.

Data collected by Research Assistants (RAs) will include:Medical history: Full history of antipsychotic use, doses, and responsePatient-rated outcome measure (PROM): Drug Attitude Inventory (DAI-10)Adverse events: Glasgow Antipsychotic Side-effect Scale for Clozapine (GASS-C). It is a modification of the GASS, a well validated side effect scale, with additional questions pertaining to common adverse effects of clozapineAdverse events: spontaneous report. The RAs will prompt for any other suspected adverse reactions and record theseAdherence: Clinician Rating Scale (CRS)Health-related quality of Life: EQ-5D-Y, a questionnaire which is used to generate quality adjusted life years (QALYs) for use in economic evaluation, as recommended by NICEService use for economic evaluation: Early Intervention Adult Service Use Schedule (EI-AD-SUS), a measure specifically designed for use in children and young adults with psychosisRecovering Quality of Life-10 items measure (ReQoL-10) [54], a measure of health-related quality of life specifically designed for users of mental health services.

Laboratory measurements will be collected at baseline and at 12 weeks. Blood tests include HbA1c, lipids, prolactin, and liver function tests. As per standard care, the clozapine arm will undergo weekly blood monitoring to check full blood count and clozapine plasma levels as per standard care.

#### Follow-up period

After the end of the trial, we will follow-up participants after 24 and 52 weeks via video-link or phone call; if this is not possible, we will retrieve information reviewing case notes. We will record medication use, spontaneous adverse events, PANSS score, CGI-I, GASS-C, EQ-5D-Y, CRS, DAI-10, ReQol-10, EI-AD-SUS.

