### Blinding

The raters for primary outcome (PANSS) and CGI-S and CGI-I will be centralised and blinded to minimise observer bias. The participants, the treating team, and the rest of the trial team will not be blinded. There will be four blinded members of the study team: two research psychiatrists, one for adult participants and the other for child participants (each with appropriate training for that age group), the Chief Investigator (CI) and Co-Chief Investigator. They will not be informed which treatment arm the participants are in and will not enquire about the participant’s treatment or side effects.

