### Statistical analysis

The Statistical Analysis Plan will be drafted within 6 months after recruitment starts and will be approved by the Data Monitoring Committee (DMC) and Trial Steering Committee (TSC) before the junior statistician sees any outcome data split by arm. The senior statistician will remain fully blind throughout the study.

We will report data in line with the CONSORT 2010 statement [57] showing attrition rates and loss to follow-up. The target estimand is the treatment policy estimand, and all primary and secondary analyses will be carried out following the intention to treat principle, incorporating data from all participants including those who do not complete treatment. Every effort will be made to follow up all participants in both arms for research assessments. The trial will be blind rated to minimize observer bias. The primary analysis will be conducted after the final 12-week follow-up assessment is completed for the final patient recruited into the study. The study team including CI and trial statisticians will be aware of the results of the primary analysis from this point. The remaining 24-and 52-week assessments will continue to be conducted blind to individual patient’s allocation. We will analyse the 24- and 52-week outcomes in a secondary analysis.

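### The case-note fallback at 24 and 52 weeks does not exempt PANSS, CGI-I or the self-report scales, yet the protocol says these assessments stay blind

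*Protocol article*

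**What the plan says.** All references are to the protocol article.

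- **Assessments, Follow-up period.** Participants are followed up at 24 and 52 weeks by video or telephone; "if this is not possible, we will retrieve information reviewing case notes. We will record medication use, spontaneous adverse events, PANSS score, CGI-I, GASS-C". The list that begins there runs on, undivided, to the EQ-5D-Y, CRS, DAI-10, ReQoL-10 and EI-AD-SUS. It does not separate items that need an interview from items that notes can supply.
- **Trial flowchart.** The same fallback appears with a purpose attached: "otherwise case notes will be reviewed to assess longer-term outcomes".
- **Statistical analysis.** After the primary analysis, the remaining 24- and "52-week assessments will continue to be conducted blind to individual" allocation. No exception is made for information taken from notes. The mixed model is then refitted with the 24- and 52-week outcomes added to the response vector, with no mention of data source.
- **Blinding.** Four people are blinded: two research psychiatrists and the two chief investigators. Of them it says: "They will not be informed which treatment arm the participants are in and will not enquire about" treatment or side effects. Participants, the treating team and the rest of the trial team are unblinded.
- **Assessments, Clinical trial.** PANSS and CGI are centralised, remote, blind assessments by research psychiatrists. The clozapine arm has weekly blood counts and plasma-level checks.

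**The concern.** The trial is open label, and blind rating is its stated protection against observer bias. A fallback to case notes that does not exclude PANSS and CGI-I leaves a route by which late ratings could be made from a source that shows treatment, while still being described as blind.

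There is also a measurement problem. PANSS and CGI-I are otherwise rated in a remote assessment by a psychiatrist. The protocol describes the DAI-10 as patient-rated, the EQ-5D-Y as a questionnaire and the ReQoL-10 as self-reported. A value reconstructed from notes is a different measurement from any of these, and the mixed model as described would not tell the two apart.

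The outcomes at stake are not marginal. CGI and EQ-5D-Y at 24 and 52 weeks are named in the secondary hypotheses, and QALYs at 52 weeks feed a secondary cost-utility analysis. Participants who cannot be reached for interview may plausibly differ from those who can.

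**Working it through.** The plan has no figure of its own on this point, so the check is mainly whether its statements can hold together.

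**1. What does the fallback cover?** The Follow-up period section exempts no item. The Trial flowchart section gives the purpose of reading notes as assessing longer-term outcomes, which is wider than recording medication use. As written, PANSS and CGI-I are not excluded.

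**2. Can notes be read blind?** Medication use is itself on the follow-up list, so whoever uses notes for that list is looking for the drug. Weekly clozapine monitoring would be expected to appear there too. That notes reveal treatment is an inference, but a strong one. No masking step is described.

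**3. Who could rate from notes?**
- If a blinded psychiatrist reads them, the treatment is likely to be exposed for that participant. If this happens at week 24, the week-52 rating is affected as well.
- If anyone outside the four blinded members reads them, that person is unblinded under the Blinding section, and the score is not the centralised blind rating.

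Neither route gives a blind PANSS or CGI-I from ordinary notes, so the unqualified blinding statement fails for any such score.

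**4. Does the item-completion rule stop it?** Measures are pro-rated only if more than 80–90% of items are completed, and are otherwise missing. This would remove sparse note-derived scores. It tests completeness, not source or blinding, so a full PANSS scored from notes would pass.

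**5. Is the primary analysis touched?** The primary outcome is PANSS at 12 weeks, before the fallback applies. The target of 260 also rests on week 12. With standardised difference 0.39, correlation 0.5 and 20% attrition (Sample size section), and assuming two-sided 5% and 90% power, which that section does not state for the primary outcome:

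n per arm = 2 × (1.960 + 1.282)² × (1 − 0.5²) / 0.39² ≈ 103.6, so 104; total 208; 208 / 0.80 = 260.

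The figure reproduces and contains nothing from 24 or 52 weeks.

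**6. Size.** If a share f of late PANSS scores came from notes, and knowledge of treatment moved their between-arm difference by b points, the estimated effect would move by about f × b. Neither quantity is in the documents. Purely as an assumed range:
- f = 5%, b = 2: 0.05 × 2 = 0.1 points, and 0.1 / 6.4 ≈ 2%.
- f = 30%, b = 6: 0.30 × 6 = 1.8 points, and 1.8 / 6.4 ≈ 28%.

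The 6.4 points is the 12-week design difference. TAU participants may start clozapine after week 12 (Discussion), so it is a yardstick of scale only and not a 24- or 52-week target.

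**The case against.** The strongest reply is that the text never says PANSS or CGI-I will be scored from notes. One sentence gives the fallback; the next lists what follow-up records. The list includes the EQ-5D-Y, DAI-10 and ReQoL-10, which notes could hardly supply, so it may describe the interview, with notes filling in medication, service use and adverse events. The rules on blind central rating point the same way. This is fair: a reader might infer that the protocol orders note-based PANSS scoring, and the documents do not support that. What stands is that the restriction is nowhere stated, the Trial flowchart wording leans the other way, and the blinding claim carries no exception.

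A reader might also infer that blind follow-up fails as a whole, or that fallback use will differ by arm. The first could apply only to participants without an interview. For the second the documents offer no evidence.

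The article condenses a full protocol that is not shown, and who abstracts notes and how they are masked may be set out there. That answers a complaint about missing detail. It does not answer a conflict between statements printed in the article.

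Finally, setting scores to missing relies on missing at random and may exchange one bias for another. That is a real cost. It is still preferable to unblinded values that are reported as blind.

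**Conclusion.** The point holds in a limited form. The Trial flowchart and Follow-up period sections permit case-note review as the fallback without exempting PANSS, CGI-I or the self-report scales. The Statistical analysis section declares the same assessments blind. Any PANSS or CGI-I actually rated from ordinary notes would be neither blind nor comparable with the interview ratings beside it in the model.

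This rests on one inference, that notes show medication and clozapine monitoring. It applies only to participants without an interview and only to the secondary 24- and 52-week analyses. The bias cannot be sized from the documents, and the 0.1 to 1.8 points shown above is an assumed illustration, not an estimate. Severity is moderate: worth correcting before late follow-up data accrue, but no threat to the primary result.

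**What to change.** Reconcile the Trial flowchart, Follow-up period and Statistical analysis sections:

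1. Limit the case-note fallback to medication use, admissions and service use, and recorded adverse events, extracted by an unblinded research assistant. This keeps the data needed for the secondary hypothesis on staying on the same medication.
2. State that blinded raters do not see case notes.
3. Treat PANSS, CGI-I, GASS-C, DAI-10, EQ-5D-Y and ReQoL-10 as missing when no interview is obtained. If any note-derived score is kept, flag its source, leave it out of the main 24- and 52-week model, and use it only in a sensitivity analysis.

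The cost is protocol wording and rater instructions, plus somewhat more missing data at 24 and 52 weeks. The mixed model handles those gaps under missing at random. The 52-week cost-utility analysis, planned on complete cases with missing data explored in sensitivity analyses, would lose some EQ-5D-Y values. The source flag must be in place before collection, because unflagged note-derived scores could not later be separated from the rest.
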